## Introduction

### Background

Exposure to potentially traumatic events and being bullied by peers or siblings in childhood constitute forms of victimization or revictimization, which may be associated with severe long-term effects on mental health [1-3], including anxiety, depression, or suicidality [4]. We include the experience of different forms of maltreatment (emotional, physical, and sexual abuse; neglect; and intimate partner violence) as well as bullying experiences in the definition of revictimization in this trial.

Given that childhood victimization leads to an increased vulnerability for subsequent revictimization in adolescence [5,6], findings highlight a strong need for evidence-based prevention programs targeting children with a history of maltreatment or bullying as a high-risk population for revictimization. Although all types of maltreatment in childhood were found to be associated with revictimization [7] and mental health, one study with adolescent girls in child welfare found that the emotional type of maltreatment showed the strongest link to revictimization in a cross-sectional study using self-report of the types of child maltreatment experienced [8]. However, when using a population sample, sexual maltreatment increased the risk for revictimization the most [7]. In a recent meta-analysis, Scoglio et al [9] identified the following risk factors in most studies on the association between sexual victimization and revictimization: risky sexual behavior, further maltreatment experiences in childhood, presence of posttraumatic stress disorder (PTSD), and emotional dysregulation. In contrast, protective factors have rarely been examined. Only parental caregiving was identified as a protective factor. Unfortunately, many of the included studies were cross-sectional, and it is not always clear which key mechanism is driving the link (eg, why the presence of PTSD is increasing risk).

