### Study Design

The EMPOWERYOU project (funded by the German Ministry of Education and Research, Project code FKZ 01KR1806D) aims to develop and optimize a web-based parenting program by using the MOST framework [22]. This study will use a 2×2×2×2 full factorial design by randomly allocating participants to 1 of 16 experimental conditions (Table 1). To estimate the main effects of the 4 intervention components and their interactions, data from all the experimental conditions will be used. For example, the effect of the component *Relationship-related risk* will be estimated by comparing the mean of the experimental conditions 1 to 8 with the mean of the conditions 9 to 16 (Table 1). Families in the first condition will not receive any experimental component but will be delivered the 2 basic intervention modules that every caregiver receives. Families will be informed that everyone may access all modules and that the sequence and timing of each module will be based on a randomization procedure.

**Table 1 table1:** Experimental intervention conditions (optimization schema).

Experimental condition	Component 1: *Watch Out*!—relationship-related risk	Component 2: *You are safe here*—relationship-related safety	Component 3: *Who am I and where do I belong?*—identity	Component 4: *My Coach*—professional support
1	Off^a^	Off	Off	Off
2	Off	Off	Off	On^b^
3	Off	Off	On	Off
4	Off	Off	On	On
5	Off	On	Off	Off
6	Off	On	Off	On
7	Off	On	On	Off
8	Off	On	On	On
9	On	Off	Off	Off
10	On	Off	Off	On
11	On	Off	On	Off
12	On	Off	On	On
13	On	On	Off	Off
14	On	On	Off	On
15	On	On	On	Off
16	On	On	On	On

^a^Not included in the intervention.

^b^Included in the intervention.

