### Sample Size Calculations

Anticipated effect sizes were estimated from the reported effect sizes for victimization and revictimization interventions, which also included (1) facilitating risk detection skills; (2) social skills, such as problem-solving or conflict management; (3) skills to build healthy relationships; and (4) the ability to reflect on own expectations that relationships will include harm [28,60,61]. We expect small to moderate effect sizes between Cohen *d*=0.28 and Cohen *d*=0.46 for the main effects of specific intervention components (component 3: 0.46, component 4: 0.28, and component 6: 0.32). Thus, a sample size of 317 was determined as necessary to detect the smallest anticipated effect size of Cohen *d*=0.28. To detect this difference with the analysis of covariance as the suggested method for component selection by the developer of the factorial design (groups=2, *df*=1, covariate=1) with 80% power at α=.10 per intervention component or interaction, a sample size of 317 is required (calculated with FactorialPowerPlan SAS Macro provided by [name] [62]). We will use an intention-to-treat approach, although only one family dropped out during the intervention period in the pilot study. In contrast, findings from the pilot study showed that 26% (4/15) of the recruited caregivers that registered for the website dropped out before the intervention. Therefore, we consider a dropout rate (before the allocation to condition) of 26%. Therefore, we aim to recruit a total of 429 families. Recruitment will be stopped as soon as we reach the sample size needed for the analysis (N=317).

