### Measures

#### Primary Measures

To investigate the primary efficacy, we will use a revictimization score derived from 2 measures: the Juvenile Victimization Questionnaire [33] and the bullying screener [34]. We will assess the child and parent reports of each measure while using the parent report for the primary outcome. The Juvenile Victimization Questionnaire is a widely and internationally used self-report measure to assess victimization in children aged 8 to 17 years. It consists of 34 items in the child version and 37 items in the parent version spanning 5 domains, namely, crime, child maltreatment, peer and sibling victimization, sexual victimization, and witnessing crime, with follow-up questions that also assess the frequency and perpetrators of the victimization events. A total of 3 supplemental items on electronic victimization will be assessed. In our study, the participants (caregiver and child) will be asked whether the child was exposed to the respective event and, if yes, whether it happened during the last 3 months (primary outcome–assessment period). The participants will respond with yes (1) or no (0), leading up to a total score, with higher scores indicating greater victimization exposure. The bullying screener [34] is a 6-item screening tool that assesses bullying as victim and offender. After the respective definition of bullying type, the participants are asked how often these things happened to the child or how often they have done this to others in the last 3 months. The participants then respond on a 4-point scale from never to a lot (*at least once a week*).

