### Statistical Analysis

#### Analyses

Before the analyses, missing data will be examined and appropriately handled using multiple imputation or full information maximum likelihood estimation. To investigate the effectiveness of each intervention component, the primary analyses will test the pre–follow-up change in children’s revictimization composite scores. The primary analysis will be conducted in an intention-to-treat sample. We will use the analysis of covariance with main and interaction effects on the primary and secondary end points. The main effects and interactions are estimated based on aggregates (each reflecting the presence or absence of a specific component) across the 16 experimental conditions. The main effects will be modeled as a fixed effect with baseline levels of an outcome as a covariate and an assumed type I error of *P*<.10 (recommended for component selection [22]). To examine the hypotheses related to mediating and moderating effects, we will use regression analyses. Mediational analyses will be conducted by analyzing the indirect effects of each component on the primary outcome via the assumed mediators (Figure 1). Moderator analyses will be modeled in steps with baseline predictors (eg, type of maltreatment) and then as a second model including interactions with the main effect by condition.

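### The primary ANCOVA adjusts only for the baseline parent-report 3-month score; two further baseline measures collected in the same web survey could be added as covariates for a modest, nearly free gain in precision

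*Protocol article*

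**What the plan says.** The Analyses section sets an analysis of covariance for the primary and secondary end points and names one type of covariate: "The main effects will be modeled as a fixed effect with baseline levels of an outcome as a covariate". The Sample Size Calculations section agrees: its inputs end with "covariate=1) with 80% power at α=.10 per intervention component or interaction, a sample size of 317 is required".

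Primary Measures defines the score from two instruments, the Juvenile Victimization Questionnaire and a bullying screener, and settles the informant: "We will assess the child and parent reports of each measure while using the parent report for the primary outcome". On the questionnaire, both informants "will be asked whether the child was exposed to the respective event and, if yes, whether it happened during the last 3 months". The bullying screener asks about the last 3 months only.

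The Data Collection section puts the first assessment at week 1 as a web survey. The Randomization and Blinding section has families told their allocation only after baseline data are complete.

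**The concern.** The single covariate is a short-window event score from one informant, so it is likely to measure a child's underlying risk with noise. Two other measures of the same construct are taken at the same survey: the child's own 3-month report, and the caregiver's answer on whether each questionnaire event occurred at all. The Background section itself argues that "childhood victimization leads to an increased vulnerability for subsequent revictimization in adolescence", which makes exposure history a natural candidate predictor.

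Precision matters because the Decision-making Process selects components first on the significance of the main effect on the primary outcome, at P<.10. The design aims at 80% power for the smallest anticipated effect, so on the plan's own terms a component with that effect is missed at the first step one time in five. In a randomized linear model, prespecified baseline covariates reduce residual variance for main effects and interactions without biasing them.

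**Working it through.** **Inputs from the article.** d = 0.28, alpha = .10, power 80%, one covariate, N = 317, and 16 conditions. Each component splits the sample in half, for example by "comparing the mean of the experimental conditions 1 to 8 with the mean of the conditions 9 to 16". Sidedness is not stated; a two-sided test reproduces N.

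**Reproducing 317.** The noncentrality is d·√(N/[4(1−R²)]). With R² = 0 and 317 − 16 − 1 = 300 error degrees of freedom, power is 0.800 at N = 317. The calculation therefore takes no credit for correlation between covariate and outcome, or else d is already on the adjusted scale. Either way the figure is right.

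**Gain from the exposure count.** The article gives no correlations, so these are assumptions:
- r1, 3-month score with follow-up: .40-.50
- r2, exposure count with follow-up: .30-.50
- r12, between the two counts: .40-.50

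R²(both) = (r1² + r2² − 2·r1·r2·r12)/(1 − r12²). The share of residual variance removed is p = (R²(both) − r1²)/(1 − r1²), and the equivalent sample size is 317/(1 − p).

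- Least gain, (.50, .30, .50): R² = (.25 + .09 − .15)/.75 = .2533; p = .0033/.75 = 0.4%; equivalent N 318.
- Middle, (.45, .40, .45): R² = (.2025 + .16 − .162)/.7975 = .2514; p = .0489/.7975 = 6.1%; equivalent N 338.
- Most gain, (.40, .50, .40): R² = (.16 + .25 − .16)/.84 = .2976; p = .1376/.84 = 16.4%; equivalent N 379.
- Outside the range, (.50, .30, .60): R² = (.25 + .09 − .18)/.64 = .25 = r1²; p = 0.

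Interval widths shrink by 1 − √(1 − p): 0.2%, 3.1% and 8.6% for the first three cases.

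**Power at N = 317, d = 0.28.** The result depends on the scale of d.

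| Case | d on adjusted scale: one covariate → with count | d on raw scale: one covariate → with count |
|---|---|---|
| Least | .800 → .802 | .890 → .891 |
| Middle | .800 → .822 | .873 → .891 |
| Most | .800 → .859 | .857 → .907 |

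The gain is about 0.1 to 6 points on the adjusted scale and 0.1 to 5 on the raw scale.

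**Adding the child report as well.** Five illustrative sets of correlations for all three covariates, again assumed, gave a combined p of 1.0% to 10.2%, equivalent to 320 to 353 families. Error degrees of freedom fall from 300 to 317 − 16 − 3 = 298.

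**The case against.** The strongest reply is that nothing here is wrong. ANCOVA on the baseline value of the outcome is a standard, valid primary model, and further covariates are optional. That stands, and it limits the point to efficiency. A related reply is that the article does not exclude other covariates and that the full list may sit in an analysis plan not shown. But the article does state a covariate, and the sample size section matches it with a count of one. If the analysis plan already adds these two, the point is met.

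Four stronger readings are tempting and not supported.

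- A reader might infer that the trial is underpowered without the extra covariates. It is not. If d is on the raw scale, the planned model already has about 86-89% power under the assumed r1; if d is on the adjusted scale, it has the stated 80%.
- A reader might infer that a lifetime version of the primary score is on file. The questionnaire item precedes the 3-month question and carries no stated time frame; reading it as ever exposed is an inference from that order. The bullying screener has no such item.
- A reader might call these strong predictors. The Background statement concerns later revictimization in adolescence. It does not say that exposure history predicts a 3-month parent-report score at ages 8 to 13 beyond the baseline score. The 3-month items are also nested within the exposure items, so substantial overlap is plausible.
- A reader might infer that a missed main effect means removal of the component. The decision process looks next at interactions and then at mediation models.

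**Conclusion.** The point holds as a low-cost improvement in efficiency. The primary model uses one baseline covariate, while two related measures from the same pre-allocation survey go unused. Validity, N = 317 and the stated 80% power are unaffected.

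The size of the gain cannot be derived from the article. It rests wholly on the assumed correlations, with about 6% of residual variance (roughly 21 families, 338 − 317) in the middle of the range. It disappears if the two counts are largely redundant. Because the cost is negligible even then, the change is still worth making.

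**What to change.** In the Analyses section, prespecify two further baseline covariates for the primary-outcome models, the same set for main effects and interactions:

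1. the child-report 3-month revictimization score;
2. the parent-report count of Juvenile Victimization Questionnaire events ever endorsed, stating that the bullying screener contributes nothing to this count.

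Fix this before the assignment is unblinded. Handle missing child reports with the multiple imputation or full information maximum likelihood already planned, and report the one-covariate model as a sensitivity analysis.

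The cost is a short protocol text change, with the ethics notification that the article requires for any protocol change, and two of about 300 error degrees of freedom. No new data are needed and the sample size does not change.

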#### Decision-making Process

We will use the “all active components criterion” [22] for the selection of component levels. This means that we plan to include the component levels of the entire set of components that are associated with a better outcome, following an a priori decision-making process: (1) main effect on the primary outcome at follow-up; (2) if no significant main effect can be found, we will consider the interaction effect; and (3) if no main or interaction effects are found, we will consider the mediation models. If we do not find any significant main effect for any of the 4 factors on revictimization, we will choose the more cost-effective component levels. Before analysis, the assignment will be blinded in the data set. After completing the decision-making process, the assignment will be unblinded.

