**Hypotheses to be examined**
Component *Watch Out!* deals with relationship-related risks, and we hypothesize that receiving this component will result in a better detection of risk signals in relationships and less risk-taking cognitions. This will lead to less relationship-related risk-taking behavior, which, in turn, will result in reductions in revictimization experiences and other secondary outcomes.Component *You are safe here* deals with relationship-related safety, and we hypothesize that receiving this component will result in a better detection of relationship-related safety signals in relationships and more emotional security. This will lead to more functional relationship behavior, which, in turn, will result in reductions in revictimization experiences and other secondary outcomes.Component *Who am I and where do I belong?* deals with the construction of identity, and we hypothesize that receiving this component will increase parental support for the child’s efforts in constructing a coherent identity. This will lead to less risk-taking behavior and more functional relationship behavior, which, in turn, will result in reductions in revictimization experiences and other secondary outcomes.Component *My Coach* deals with professional support, and we hypothesize that professional support from a parent coach who is facilitating each component will result in higher program adherence or engagement, which will yield larger intervention effects on the primary and secondary outcomes than without professional support.We hypothesize that there will be an interaction effect between the relationship risk and relationship safety components. When both components are present, the effect will be larger compared with when only one of them is present.We hypothesize that there will be an interaction effect between each component and the professional support component such that with professional support, the effects of each component will be larger than those without professional support via greater adherence of the caregiver.

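### The component-selection rule gives two incompatible instructions when no main effect is significant, and never lets an interaction modify a choice made on a main effect

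*Protocol article*

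**What the plan says.** The protocol article, under Decision-making Process, adopts the all-active-components criterion and describes the selection as fixed in advance. The steps are:

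- "1) main effect on the primary outcome at follow-up"
- "2) if no significant main effect can be found, we will consider the interaction effect"
- "3) if no main or interaction effects are found, we will consider the mediation models"

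The sentence directly after them reads: "If we do not find any significant main effect for any of the 4 factors on revictimization, we will choose the more cost-effective" component levels.

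Three other places bear on this. Analyses fits an analysis of covariance with main and interaction effects, each judged at P<.10. Sample Size Calculations claims 80% power at α=.10 for each component or interaction. The hypotheses textbox predicts four interactions. For the first it states: "We hypothesize that there will be an interaction effect between the relationship risk and relationship safety components". The other three are between the coach and each content component.

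**The concern.** The closing cost sentence has the same trigger as step 2, namely no significant main effect, but prescribes a different action. Its condition does not mention interactions or mediation, so on its wording it is not a fourth step that applies only after the first three have failed.

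There is a second gap. Interactions enter only where no main effect is significant, and no step returns to a component that has passed step 1. The plan therefore powers and hypothesises interactions but gives them no role in the selection once main effects appear.

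The article calls choosing the best candidates the ultimate goal, and the chosen package goes on to a phase 3 trial. Two analysts with identical results could each follow the text and choose different packages, which is what a rule fixed in advance should prevent.

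**Working it through.** **Inputs from the article.** N = 317, d = 0.28, 80% power and α = .10 per component or interaction (Sample Size Calculations). Sixteen conditions in blocks of 16, so every main effect and interaction contrast is split about 1:1 (Randomization and Blinding). Four hypothesised interactions (hypotheses textbox).

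**Assumptions.** SD 1, two-sided tests, and contrasts that are close to independent because the design is balanced. An interaction of size d is half the difference between a component's effects at the two levels of its partner, so it has the same standard error as a main effect.

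**1. The plan's own figure.** Total N = 4 × (1.645 + 0.842)² / 0.28² = 315.4, that is 158 per level or 316. The noncentral t version gives 317 with power 0.800. The stated figure reproduces, and equal power for main effects and interactions follows. (One-sided .10 would give 230, so two-sided testing is implied.)

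**2. Reaching the contradictory branch.** If no component has any effect, P(no significant main effect) = 0.9⁴ = 0.656.

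**3. Direct collision under the same null.** This is no significant main effect together with at least one significant interaction.
- Four hypothesised interactions: 1 − 0.9⁴ = 0.344, and 0.656 × 0.344 = 0.226.
- All six two-way interactions: 0.656 × (1 − 0.9⁶) = 0.307.
- All eleven interactions: 0.656 × (1 − 0.9¹¹) = 0.450.

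A simulation of the 16-condition design (317 families, all 15 effects fitted, no baseline covariate, 4,000 runs) gave 0.222, 0.305 and 0.442.

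**4. Collision with one true interaction of d = 0.28 and no main effects.** 0.9⁴ × 0.80 = 0.525. This is a lower bound, because other interactions can also be significant by chance. The scenario is a crossover: the component's effect is +0.28 at one level of its partner and −0.28 at the other. If instead two components worked only together (0.56 SD jointly), each main effect would also be 0.28, and the collision would be rare: 0.2 × 0.2 × 0.9² × 0.80 = 0.026.

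**5. Interaction ignored after a significant main effect (assumed effects).** A alone 0.56, B alone 0.56, both together 0.56.
- Main effect of each = (0.56 + 0)/2 = 0.28.
- Interaction = (0 − 0.56)/2 = −0.28.
- P(both main effects significant) ≈ 0.80 × 0.80 = 0.64 (simulated 0.644 in 2,000 runs).
- In the simulation the interaction was significant in 81% of trials. Both components were kept and the interaction was significant in 52%.

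Step 1 keeps both, although the second adds 0.56 − 0.56 = 0.

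**6. Scope of the phrase about no significant main effect.** The text does not say whether this is judged per component or across all four. Take the across-all reading, one component with a main effect of 0.28, and a separate component-by-coach interaction of 0.28. P(some main effect significant) = 1 − 0.2 × 0.9³ = 0.854, and × 0.80 = 0.68 (simulated 0.69). In that share of trials the interaction is significant but never considered.

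**The case against.** The natural defence is that the cost sentence closes the paragraph as a fallback once steps 1 to 3 have produced nothing. That may well be the intention, but the sentence names main effects only and no other section supplies the missing condition. It is also fair that more cost-effective is not simply cheaper, since cost-effectiveness weighs effect as well. This softens the opposition but does not say whether a significant interaction counts.

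On interactions, the hypothesised ones are synergistic. Where two components both show main effects and reinforce each other, keeping both is right and the rule does no harm. This stands. So does the point that the all-active-components criterion deliberately favours inclusion, and that a later randomised trial will test the package.

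Several stronger readings are tempting but not supported:

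- A reader might infer that the rule will select a harmful or inferior package. The antagonism in step 5 is assumed, and even there the pair does as well as one component. The package is redundant, not worse.
- A reader might take 66% as the frequency of conflicting decisions. It is only the chance of entering the branch. The direct collision with a hypothesised interaction is about 23% under the null.
- A reader might object that step 2 does not list the eligible interactions. That is detail an article can leave to a fuller plan.
- A reader might see mediation as undefined, because the secondary objectives place it on secondary outcomes. Analyses specifies "analyzing the indirect effects of each component on the primary outcome via the assumed mediators", and the four mediation questions also concern revictimization. Both sets of models can be run.

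Finally, masking the assignment in the data set until the decision is complete limits motivated choice, but it does not tell the analyst which instruction to follow.

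**Conclusion.** The contradiction is in the text and needs no assumption: with no significant main effect, steps 2 and 3 and the cost sentence cannot both be followed when an interaction or a mediation model favours a component. The collision with a hypothesised interaction has probability about 0.23 under the global null and at least 0.52 under one crossover interaction of d = 0.28. It is small (about 0.03) under strong pure synergy, because main effects then appear as well.

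The second defect, that interactions cannot modify a choice made at step 1, is also textual. Its consequence depends on an antagonistic interaction, whose size the article does not give. The 64% figure is an illustration and not a forecast.

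The probabilities assume two-sided .10 tests and near-independent contrasts. The estimates, the tests and N = 317 are unaffected. This should be fixed, because it concerns which package can be selected, but it does not undermine the trial's data.

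**What to change.** Replace the rule in Decision-making Process with one ordered sequence:

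1. Provisionally include each component with a favourable main effect on the primary outcome at p<.10.
2. In all cases, whether or not main effects are significant, examine the four hypothesised interactions (risk by safety; coach by each content component). Where one is significant, choose among the combinations concerned by model-predicted means on the primary outcome. Take the less costly combination when the added component gives no predicted gain.
3. For components still undecided, consult the mediation models on the primary outcome.
4. Choose the more cost-effective level only when steps 1 to 3 give no reason to include the component.

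The tie rule in step 2 is needed. In the 0.56 SD example the predicted means are equal, and without it the redundant component would stay because step 1 had already admitted it. Estimated means seldom tie exactly, so the team should also state in advance how small a difference counts as no gain; the article gives no figure for this.

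The cost is a few lines of wording before any outcome analysis, with no new data and no change in sample size. The downside is less freedom to use other interactions in the selection. Risk by identity and safety by identity, for example, would remain exploratory.
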